**Methods:**

Two mixed-methods randomized controlled trials will be conducted. In Study 1, participants will be randomly assigned to one of three groups (HIFT, MBSR, QG) using a 1:1:1 ratio. Psychological, cognitive, physical, physiological, and biological measures will be evaluated two weeks before and after the interventions. The interventions include three weekly sessions for 12 weeks. Subsequently, a follow-up will be conducted 12 weeks after the intervention to assess psychological well-being. Study 2 is a proof-of-concept study in which VR interventions will be co-designed with input from university students and professionals. Twelve participants from each study will also complete semi-structured interviews to explore their experiences and perceived impact.

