**Fig 1 pone.0328538.g001:**
[figure not shown]
Schedule of enrolment, interventions, and assessments. HIFT: High-Intensity Functional Training, MBSR: Mindfulness-Based Stress Reduction, QG: Qigong, VR: Virtual Reality.

The project includes two distinct studies:

**Study 1 delves into online physical exercise and mind-body interventions.** Its primary objective is to evaluate the effectiveness of HIFT, MBSR, and QG on the psychological well-being and cognitive functions of university students and to uncover potential mediators and moderators. Specifically, Study 1 aims to explore: (1) the effectiveness of HIFT, MBSR, and QG interventions on the psychological well-being and cognitive functions of university students; (2) the intervention-induced changes in physical aspects (physical activity and fitness status), mental aspects (mindful thinking and sleep quality), and physiological stress markers (heart rate variability [HRV]), and their potential mediating effects on psychological well-being and cognitive outcomes; (3) the intervention-induced changes in the microbiota and its potential mediating effect on psychological well-being and cognitive outcomes; and (4) the potential moderating effects of demographic factors (sex and age) and individual factors (cognitive reserve and general intelligence) on intervention-induced changes in psychological well-being and cognitive outcomes (see Fig 2).

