**Fig 2 pone.0328538.g002:**
[figure not shown]
Key variables of interest in the YoungFitT study. HIFT: High-Intensity Functional Training, MBSR: Mindfulness-Based Stress Reduction Therapy, QG: Qigong, VR: Virtual Reality, HRV: Heart Rate Variability.

The key hypotheses for this objective are: (1) All three interventions will positively affect psychological well-being and cognitive functions at 12 weeks compared to baseline, with each intervention showing a specific profile of outcomes (HIFT: more cognitive gains; MBSR: more psychological gains; QG: moderate benefits in both areas). These positive effects are expected to persist at the 12-week follow-up; (2) All interventions are expected to induce changes in physical components (increased physical activity and fitness status), mental components (enhanced mindful thinking and sleep quality), physiological stress markers (increased HRV), and microbial composition (increased diversity), which will mediate improvements in psychological well-being and cognitive outcomes; (3) Sociodemographic factors (sex and age) and individual factors (cognitive reserve and general intelligence) will moderate changes in outcomes from pre- to post-intervention.

**Study 2 focuses on VR-based physical exercise and mind-body interventions.** The primary objective of this proof-of-concept study is to test the feasibility and preliminary effectiveness of VR-based HIFT, MBSR, and QG interventions on the psychological well-being and cognitive functions of university students. The specific objectives of this study include: (1) Generating virtual environments for HIFT, MBSR, and QG interventions; (2) Evaluating the usability, acceptability, and feasibility of these VR interventions; (3) Studying the effectiveness of VR interventions as depicted in Fig 2; and (4) Exploring the effects and adherence of these VR-based physical exercise and mind-body interventions compared to non-VR interventions.

It is hypothesized that: (1) All VR interventions will positively affect psychological well-being and cognitive functions after 12 weeks, with each intervention displaying distinct outcomes (HIFT: cognitive gains; MBSR: psychological gains; QG: moderate benefits); and (2) VR-based interventions will yield better adherence and greater benefits compared to non-VR interventions.

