#### Study status and timeline.

Participant recruitment is anticipated to occur in three waves for Study 1 (February 2024, February 2025, and September 2025) and three waves for Study 2 (September 2025, December 2025, and February 2026), although this schedule may vary depending on study needs. Each recruitment wave will last approximately four months. Recruitment began on 5 February 2024 and is expected to be completed by February 2026. Data collection is actively being conducted and is anticipated to conclude by June 2026. We estimate that results will be analyzed and reported by August 2026.

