### Randomization

In Study 1, an independent researcher will use a software-generated random sequence to allocate participants into three groups at a 1:1:1 ratio for each wave (Fig 3). The randomization list will be securely generated and stored on a university server. While the research team will be aware of the allocation sequence, participants will remain unaware of their group assignment until the intervention. In Study 2, participants will be assigned to one of three intervention groups through sequential cohort assignment based on recruitment order. Potential biases in group composition will be mitigated by monitoring baseline characteristics across groups and adjusting for these in subsequent analyses. Outcome assessors will be blinded to group allocation through the use of coded identifiers to ensure unbiased assessments. To prevent unintentional disclosure, participants will be reminded not to discuss their group allocation during post-intervention assessments. To assess blinding success, outcome assessors will guess participants’ group assignments after the final evaluation. The proportion of correct guesses will be compared to the 33% chance level using a chi-square goodness-of-fit test with one degree of freedom. Data analysts will conduct analyses without access to group allocation information, thereby ensuring the integrity of the results.

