#### Virtual reality-based physical exercise and mind-body interventions.

The immersive VR system will be co-designed through a structured focus group involving six participants, consisting of university students and professionals. The focus group aims to explore the integration of well-being interventions into VR environments. One session will be conducted online via Zoom and will last approximately 60 minutes. A moderator will guide the discussions using a structured interview script (S4 File). The discussions will revolve around key questions concerning the feasibility, advantages, and challenges of implementing these practices in a VR environment. The sessions will be recorded using Zoom’s built-in recording feature, with participants’ prior consent. The recordings will then be transcribed and analyzed thematically. All responses will remain anonymous, and data will be securely stored on the university’s server. Session characteristics (e.g., frequency, duration) will be informed initially by existing literature on VR-based well-being interventions and further adapted throughout the co-design process to determine the optimal configuration for delivering VR-based interventions. Expert evaluations and usability assessments will ensure that the intervention meets user needs and well-being objectives. A computer science technician will develop the VR environments using Unity, a widely used real-time 3D development engine [77]. These environments will feature realistic avatars representing the participants. The proficient instructors who conducted the training in Study 1 will also be involved in developing the VR programs for Study 2. Participants will be provided with Meta Quest 3S headsets (Meta) to train remotely, fully utilizing the potential of VR through embodiment, body tracking, music, and immersive environments such as natural settings.

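### Study 2 hypothesis 2 predicts that VR beats non-VR, but its only comparator is a separate, largely non-concurrent study with no randomisation between the two, and Study 2 is itself labelled randomised although it is not

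*Protocol article*

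**What the plan says.** All references are to the protocol article.

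- **Objectives and hypotheses, Study 2.** Hypothesis 2 is directional: "VR-based interventions will yield better adherence and greater benefits compared to non-VR interventions". The matching objective 4 is softer: "Exploring the effects and adherence of these VR-based physical exercise and mind-body interventions compared to non-VR interventions".
- **Objectives and hypotheses, opening.** "The project includes two distinct studies". Study 1 holds the three online arms and Study 2 the three VR arms. Neither holds both kinds.
- **Randomization.** Study 1 uses a "software-generated random sequence to allocate participants into three groups at a 1:1:1 ratio for each wave". In Study 2, "participants will be assigned to one of three intervention groups through sequential cohort assignment based on recruitment order".
- **Abstract, Methods.** "Two mixed-methods randomized controlled trials will be conducted". The Study design section likewise describes the whole two-phase project as an RCT.
- **Study status and timeline.** Study 1 recruits in waves from February 2024, February 2025 and September 2025. There are "three waves for Study 2 (September 2025, December 2025, and February 2026"). Each wave lasts about four months, and the dates may change.
- **Virtual reality-based interventions.** "Session characteristics (e.g., frequency, duration) will be informed initially by existing literature on VR-based well-being interventions", and are then adapted during co-design.
- **Eligibility criteria.** One exclusion, for severe dizziness and similar problems with VR use, applies to Study 2 only.
- **Intervention adherence.** Instructors log class attendance in Study 1, where only independent practice is self-reported. Study 2 participants log their own attendance, which a researcher then reviews.
- **Discussion.** Study 2 findings are to be treated as preliminary. The reason given is the small sample.

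**The concern.** A directional statement that VR does better than non-VR invites a causal reading. This design cannot separate the effect of VR from the other things that change with it: calendar period, who volunteers for a VR study, an extra exclusion, a session format not yet fixed, and the way attendance is recorded. Adherence is half of the hypothesis, so the recording difference could by itself produce an apparent gain or loss.

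The randomised label adds to the problem. A reader of the abstract would take Study 2 to be a randomised trial and could carry that assurance over to the VR contrast. Study 2 is not randomised between its own groups, and nothing in the project is randomised between VR and non-VR.

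At stake is what may be concluded about VR. Study 1's own three-arm randomised comparison is untouched.

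**Working it through.** **1. Is there a randomised or concurrent comparator?**

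| Feature | Study 1 (non-VR) | Study 2 (VR) |
|---|---|---|
| Allocation | Random, 1:1:1, within wave | Sequential cohorts by recruitment order |
| Planned size | 177 (59 per group) | 45 (15 per group) |
| Wave starts | Feb 2024, Feb 2025, Sep 2025 | Sep 2025, Dec 2025, Feb 2026 |
| Eligibility | Common criteria | Common criteria plus a VR-related exclusion |
| Session frequency and duration | Fixed | To be set by literature and co-design |
| Attendance | Classes logged by instructors | Logged by participants |

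Using Study 1 as comparator is an inference, but the article offers no other non-VR group. Two of the three Study 1 wave starts precede all Study 2 recruitment, and two of the three Study 2 wave starts follow the last Study 1 wave start. With waves of about four months, the September 2025 Study 1 wave could run to about January 2026 and overlap part of the December 2025 Study 2 wave. Recruitment is therefore largely, not wholly, non-concurrent.

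**2. Does the plan's own sample-size figure bear on this?** It reproduces. For three groups, f = 0.25 and two-sided 0.05, N = 159 gives critical F = 3.054 and power 0.805, and 159/0.9 = 176.7, so 177. That calculation is for the Study 1 omnibus test. No figure is given for VR versus non-VR.

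**3. What could a between-study shift do?** The article gives no shift, so the values below are assumptions. In SD units, with no covariate adjustment and no dropout:

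- Pooled: SE = sqrt(1/45 + 1/177) = 0.167.
- One modality: SE = sqrt(1/15 + 1/59) = 0.289.

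The probability of a two-sided p < 0.05 with no VR effect and a shift b is approximately Φ(b/SE − 1.96) + Φ(−b/SE − 1.96). The noncentral t result follows the slash.

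| Assumed shift b | Pooled, 45 v 177 | One modality, 15 v 59 |
|---|---|---|
| 0.2 SD | 22.4% / 22.2% | 10.6% / 10.5% |
| 0.3 SD | 43.5% / 43.2% | 18.0% / 17.6% |
| 0.5 SD | 85.0% / 84.7% | 40.9% / 40.0% |

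The nominal rate is 5%. For the same shift, the larger comparison goes wrong more often. A caveat about sample size therefore does not cover bias.

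**4. Would restricting to the shared wave solve it?** Assume equal waves, and Study 2 cohorts that coincide with waves. September 2025 would then hold about 45/3 = 15 VR participants, possibly all of one modality, against about 59/3 ≈ 20 Study 1 participants of that modality. SE = sqrt(1/15 + 1/20) = 0.342, so the 95% interval is about ±0.67 SD and the difference detectable with 80% power is about 0.99 SD. The other two VR modalities would have no comparator in that wave. Adjusting for wave as a fixed effect meets the same limit, because it can separate VR from time only where waves overlap.

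**The case against.** The strongest reply is that the article plans no superiority test of VR. Objective 4 is worded as exploration, the Study 2 primary objective concerns feasibility and preliminary effectiveness, the Sample size section calls it proof-of-concept, effect sizes are to be reported to help interpretation, and the Discussion treats the findings as preliminary. A cross-study model may sit in an analysis plan that is not shown, so its absence is no fault. This stands. A reader might infer that the investigators intend a significance test and a formal superiority claim; no section says so.

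Several mitigating features also stand. Recruitment is scheduled to avoid peak academic periods. Both studies have September and February waves, so academic term is partly matched. The general ANCOVA already includes baseline score, sex and age. Session format can be seen as part of the VR package.

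The figures above are open to a fair criticism too. They rest on assumed shifts, and the pooled contrast is one the article never specifies. A reader might take the 85% as this trial's error rate; the documents do not support that.

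What does not stand is the view that these points dispose of the matter. The directional hypothesis remains beside the exploratory objective. The baseline adjustment promised under Randomization is written for the Study 2 groups, and adjustment for measured covariates cannot remove differences in calendar time, self-selection or attendance recording. The Discussion's caveat is about sample size alone. No analysis plan can supply randomisation that the design lacks.

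**Conclusion.** The point holds as one about wording, labelling and interpretation. Hypothesis 2 predicts a VR advantage that this design can describe but cannot attribute to VR, and the Abstract and Study design sections apply a randomised label to Study 2 that the Randomization section contradicts.

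The size of any bias is unknown. The illustrations range from about 11% to 85% false-positive findings, depending on an assumed shift of 0.2 to 0.5 SD and on whether modalities are pooled. They show direction and sensitivity and do not estimate this trial's error.

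The conclusion rests on one inference, that Study 1 is the comparator, which follows from Study 2 having no non-VR group. It does not imply that recruitment is wholly non-concurrent, or that Study 2's feasibility aims are affected. The change should be made because it is cheap and limits what may be concluded about VR.

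**What to change.** 1. Reword hypothesis 2 as an exploratory, non-randomised comparison, in line with objective 4, and name Study 1 as the comparator.
2. Report VR minus non-VR differences by modality with 95% confidence intervals, adjusted for baseline score, sex and age, with no claim that VR caused the difference.
3. Show the overlapping September 2025 wave only as a sensitivity analysis, noting that it may contain few VR participants or a single modality. It should not be the main comparison set.
4. Compare adherence on a measure recorded the same way in both studies or, failing that, state the recording difference beside the result.
5. Remove the randomised label from Study 2 and from the VR contrast in the Abstract and Study design sections, so that they agree with the Randomization section.
6. Add calendar time, self-selection, eligibility and session format to the limitations, separately from sample size.

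The cost is small: wording, a short analysis statement and, if attendance recording is aligned, a minor procedural change. No new outcome data are needed. The downside is a more modest claim about VR.

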### Qualitative objectives and research questions

The qualitative component of the YoungFitT project aims to complement the quantitative findings by exploring participants’ perspectives and insights regarding their experiences with the interventions. The specific qualitative objectives are: (1) to explore participants’ experiences and perceived effects of the HIFT, MBSR, and QG interventions; and (2) to identify barriers and contextual factors influencing participant engagement and adherence to the interventions (e.g., motivational challenges, instructor support, and environmental influences).

The corresponding research questions are: (1) How do participants describe their experiences and perceived benefits from participating in the interventions? and (2) What challenges and contextual factors affect participants’ ability to engage with and adhere to the program?

## Materials and methods

### Study design

The YoungFitT project is a prospective, three-arm, parallel, single-blinded RCT mixed-methods study planned to be conducted in two phases, as illustrated in Fig 3. Study 1 will begin first, followed shortly by Study 2. Both studies adhere to the SPIRIT guidelines [66] (See S1 File). The Faculty of Psychology at the University of Barcelona will lead this interdisciplinary project, integrating expertise in neuropsychology, sports science, and computer science. The study protocol has been registered at ClinicalTrials.gov (identifier: NCT06406283) and approved by the institution’s Bioethics Committee (IRB number: IRB00003099; protocol code: CER112327) on October 18, 2023 (See S2 and S3 Files). It also complies with the ethical standards outlined in the Declaration of Helsinki. Eligible participants who agree to take part in the study will provide written informed consent. A member of the research team will obtain the signed consent form prior to conducting any baseline assessments. Protocol amendments will be updated on ClinicalTrials.gov and shared with regulatory bodies if necessary.

**Fig 3 pone.0328538.g003:**
[figure not shown]
Study design of the YoungFitT project. HIFT: High-Intensity Functional Training, MBSR: Mindfulness-Based Stress Reduction, QG: Qigong, VR: Virtual Reality.

#### Study status and timeline.

Participant recruitment is anticipated to occur in three waves for Study 1 (February 2024, February 2025, and September 2025) and three waves for Study 2 (September 2025, December 2025, and February 2026), although this schedule may vary depending on study needs. Each recruitment wave will last approximately four months. Recruitment began on 5 February 2024 and is expected to be completed by February 2026. Data collection is actively being conducted and is anticipated to conclude by June 2026. We estimate that results will be analyzed and reported by August 2026.

### Eligibility criteria

Participants will be included in the YoungFitT study if they meet the following inclusion criteria: (1) are university bachelor’s or master’s students, (2) are aged between 18 and 25 years, and (3) have proficiency in either Catalan or Spanish. Participants will be excluded from the study based on any of the following criteria: (1) having injuries that prevent exercise, (2) a history of severe neurological or psychiatric diseases (e.g., schizophrenia or bipolar disorder), (3) a history of alcohol or drug abuse, or (4) conditions causing severe dizziness or related issues affecting VR use (Study 2).

### Recruitment

Participants will be recruited through various strategies, including promotional flyers placed in faculty areas, in-class announcements, email outreach, social media and messaging platforms (e.g., X, Bluesky, Instagram, LinkedIn, and WhatsApp), as well as snowball sampling. To minimize the influence of seasonal or academic stressors (such as exams or holidays), recruitment periods will be strategically scheduled to avoid peak academic times. Interested university students will receive phone verbal explanations regarding the study. Participants will be informed about the study objectives, inclusion and exclusion criteria, the details of study interventions, and their probability of being allocated to each intervention group. Participants will also be informed about the voluntary nature of their involvement and their right to withdraw from the project at any point. Participants who complete the follow-up assessment will receive compensation of 30 euros.

### Randomization

In Study 1, an independent researcher will use a software-generated random sequence to allocate participants into three groups at a 1:1:1 ratio for each wave (Fig 3). The randomization list will be securely generated and stored on a university server. While the research team will be aware of the allocation sequence, participants will remain unaware of their group assignment until the intervention. In Study 2, participants will be assigned to one of three intervention groups through sequential cohort assignment based on recruitment order. Potential biases in group composition will be mitigated by monitoring baseline characteristics across groups and adjusting for these in subsequent analyses. Outcome assessors will be blinded to group allocation through the use of coded identifiers to ensure unbiased assessments. To prevent unintentional disclosure, participants will be reminded not to discuss their group allocation during post-intervention assessments. To assess blinding success, outcome assessors will guess participants’ group assignments after the final evaluation. The proportion of correct guesses will be compared to the 33% chance level using a chi-square goodness-of-fit test with one degree of freedom. Data analysts will conduct analyses without access to group allocation information, thereby ensuring the integrity of the results.

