### Confidentiality and data access

Each participant will be assigned a unique alphanumeric code based on their order of inclusion to ensure confidentiality and privacy throughout the study. The Principal Investigator and Project Manager will maintain a confidential record linking each participant to their assigned code. All trial data will be anonymized and stored in a secure university database dedicated to the project, accessible only to authorized members of the research team. Once the database is complete, it will undergo a quality control process to verify its accuracy and integrity.

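### As written, the Study 1 allocation sequence is known to the research team, a member of which takes consent, so allocation concealment is not secured

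*Protocol article*

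**What the plan says.** All of this concerns Study 1 of the protocol article.

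- **Generation (Randomization):** "an independent researcher will use a software-generated random sequence to allocate participants into three groups at a 1:1:1 ratio for each wave".
- **Storage (Randomization):** "The randomization list will be securely generated and stored on a university server".
- **Who knows the sequence (Randomization):** "While the research team will be aware of the allocation sequence, participants will remain unaware of their group assignment until the intervention". Only participants are kept unaware; no member of the team is excepted.
- **Who takes consent (Study design):** "A member of the research team will obtain the signed consent form prior to conducting any baseline assessments".
- **Blinding after allocation (Randomization):** "Outcome assessors will be blinded to group allocation through the use of coded identifiers to ensure unbiased assessments", and "Data analysts will conduct analyses without access to group allocation information, thereby ensuring the integrity of the results".
- **Participant codes (Confidentiality and data access):** "Each participant will be assigned a unique alphanumeric code based on their order of inclusion".

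The article does not say when a wave's list is generated or opened relative to enrolment and baseline testing.

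**The concern.** Concealment means that whoever decides to enrol a person cannot know that person's arm beforehand. It is separate from blinding, which operates after assignment. Here the plan does more than leave concealment unmentioned: it states that the research team knows the sequence, and it has a member of that team take consent.

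Someone who can foresee an assignment may, without intending to, encourage, delay or discourage a particular student. The three programmes are plainly different, and the article's hypotheses give each its own expected profile, so staff could hold views on who suits which. One primary outcome, the DASS-21, is self-reported, so motivation, distress or a liking for a given activity could bear on it directly. The planned ANCOVA adjusts for baseline score, sex and age, with further covariates possible. That handles imbalance those variables capture and leaves the rest.

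A second difficulty lies within the same section. It says that the team knows the sequence, and then that assessors and analysts lack allocation information.

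**Working it through.** **Design figures, for context.** For a one-way ANOVA with three groups, f = 0.25, α = 0.05 and N = 159, the critical F is 3.054 and power is 0.805. Dropout: 159 / (1 − 0.10) = 176.7, rounded up to 177, or 59 per group. The plan's figures reproduce. Concealment changes neither N nor power, so the point rests on the text.

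**Step 1: does the team that knows the sequence overlap with those who enrol?** The Randomization section attributes knowledge to the research team without exception. The Study design section gives consent to a member of that team. The overlap at consent is therefore in the text. It is not in the text for other enrolment tasks: the Recruitment section describes telephone explanations without naming the caller, and no section says who judges eligibility or arranges baseline visits.

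**Step 2: do the stated safeguards conceal the sequence?**

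| Safeguard | What it protects | Conceals upcoming assignments from those who enrol? |
|---|---|---|
| Independent, software-generated list | How the list is made | No, if the team then knows it |
| Secure server storage | The list against outsiders | No, if the team then knows it |
| Participants unaware until the intervention | Participants' own choices before the start | No |
| Blinded assessors and analysts | Measurement and analysis | No; it acts after allocation |

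**Step 3: is the section consistent with itself?** The team's knowledge and the blinding of assessors and analysts can both be true only if those people are outside the team that knows the sequence. The article does not say that they are. The coding rule sharpens this: if the list runs in order of inclusion and the code does too, position in the list gives the arm. Coded identifiers would then not blind anyone who holds the list.

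**Step 4: can the bias be sized?** Only by assumption. If a fraction q of one arm is steered in with a prognosis better by d SD, and the reverse happens in a second arm, the unadjusted contrast shifts by 2 × q × d.

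- q = 3/59, d = 0.5: 2 × 0.051 × 0.5 = 0.05 SD.
- q = 6/59, d = 1: 2 × 0.102 × 1 = 0.20 SD.
- A whole wave allocated after enrolment and baseline testing: about zero, because no assignment can be foreseen.

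Neither q nor d is in the document, mirror-image steering is itself an assumption, and the figures precede covariate adjustment. They show how far the answer depends on unstated inputs; they do not estimate the bias.

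**Step 5: what could a by-wave analysis show?** If the three waves are equal (assumption), each has 177/3 = 59 participants, about 19.7 per arm. The standard error of one unadjusted between-arm contrast within a wave is √(2/19.7) = 0.32 SD. For the difference in that contrast between two waves it is 0.32 × √2 = 0.45 SD. Shifts of the size in Step 4 would not be detected reliably.

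**The case against.** The strongest reply is that the sentence is loosely worded and the procedure sound. An independent researcher allocates by wave, participants learn their group only when the intervention begins, sessions run in groups of 15, and baseline testing falls in the two weeks before the start. This fits allocating a complete wave after enrolment, with the sequence meaning assignments already made. There would then be no next assignment to foresee. Likewise, the specific statements on assessors and analysts, and the planned test of assessors' guesses, can be read as limiting the general phrase about the team. Finally, all three arms are active with different expected benefits, so no one arm is an obvious target for steering.

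Much of this stands as a limit on the point. A reader might infer that every next assignment is fully predictable, but that needs a list made before enrolment and used in order, which the article does not state. A reader might also infer that the same team telephones candidates, judges eligibility and schedules baseline visits; only consent is assigned to it. Nor is blinding of assessors or analysts shown to fail.

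The reply does not rescue the sentence. The wave-wise reading is no more confirmed than the other, and under either the statement that the team knows the sequence needs correcting. Nor is this detail that an article may leave to the full protocol, since the article states the arrangement.

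**Conclusion.** The point holds in a limited form. The text is incompatible with secured allocation concealment in Study 1, because it gives knowledge of the sequence to the research team and consent to a member of that team. Selection bias is possible. Its size is unknown, and it would be small if each wave were complete and baseline-tested before its list was generated or opened. The conflict with assessor and analyst blinding is conditional: it disappears if those people are outside the team that knows the sequence.

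The document does not support concluding that the arms are biased by any given amount, or that the waves already enrolled were unconcealed. What was done in those waves has to be asked first. The point does not extend to Study 2, which assigns by sequential cohort and raises a separate question.

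The sentence should be corrected whichever reading is true, because every between-arm comparison in Study 1 relies on the comparability that concealment protects.

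**What to change.** Replace the sentence in the Randomization section with wording to this effect:

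> Only the independent researcher has access to the sequence. Assignments, individually or per wave, are released to the staff who deliver the interventions only after consent, eligibility and baseline assessment are complete. Outcome assessors and analysts have no access.

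Restrict access to the list accordingly for the remaining Study 1 wave, scheduled for September 2025 in an article published in August 2025.

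For the earlier waves (planned for February 2024 and February 2025), report who had access to the list and when. If any wave was enrolled with the sequence known, report a sensitivity analysis by wave and state its limited power.

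If the sentence was meant to describe knowledge of assignments after randomisation, correct it to say so.

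The cost is a short text change, a change of access rights, and an account of past access, plus one additional analysis if it proves necessary. The independent researcher is already in place, and the sample size does not change. On the published schedule, tighter access can protect only the third of the three Study 1 waves; the earlier two can only be documented.
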